### Sample size calculation

With an expected prevalence of 4,5 % HARMs in 12 months within the high-risk population [26], we expect an effect of 50 % reduction of HARMs [1]. To show a statistically significant difference between the intervention group A and control group C, we include ten practices, with a total of 45.000 patients, in each group. As 6,4 % of patients in an average GP practice are part of the high risk elderly population [26], this means that in each arm at least 2850 high risk patients are included. This is based on an alpha of 0,05 and a power (1-beta) of 0,8.

### Qualitative study

In order to assess the feasibility of introducing a NDP in general practice, parallel to the POINT study qualitative data hereon is systematically collected. Semi-structured interviews with participating GPs and NDPs are conducted, and their views are described. Patients who are seen by a NDP are asked about their perceptions and experiences, using anonymised questionnaires. Hereby, conditions that hinder or facilitate the introduction of a NDP in general practice in the Netherlands may be identified.

### Privacy and informed consent/Ethical approval

Based on the Dutch law for patient data protection, this study was exempt of formal medical-ethical approval by the Medical Ethical Committee University Medical Centre Utrecht. (METC protocol number 13-432C).

## Discussion

The POINT study aims to improve safety of pharmacotherapy in primary care, by introducing a non-dispensing pharmacist as a member of the primary care team in the Netherlands. This intervention aims to improve pharmaceutical care at both patient level and organisational level. Therefore, it may be more effective than a singular intervention, such as current medication reviews. A comparison will be made with two existing models of pharmaceutical care provision in primary care. This comparison will demonstrate whether the introduction of the NDP is more effective in improving the quality and safety of pharmacotherapy than existing care models.

Several methodological challenges were faced during the design of the POINT study.

### Choice for the design

Despite the fact that a randomised controlled trial is the preferred design to evaluate the effect of an intervention, we thoughtfully chose to use a non-randomised model. In our opinion, willingness of all participating parties to improve pharmaceutical patient care is a key condition for the implementation of this intervention to succeed. This has been recognised before, during the implementation of a pharmacist in primary care in Canada [14]. Therefore, general practices participating in the intervention group of this study are selected instead of randomly allocated to one of three research arms.

This selection, of course, has disadvantages. Once proven effective, the broad implementation of this new function might be challenging because of the high standards we set for participating practices in this study. In addition, selection of motivated general practices might mask the effect of the intervention. As these practices are motivated to improve pharmaceutical care, standard pharmaceutical care might be better than average beforehand, leaving little room for improvement. By including pre-post analyses, we attempt to obviate this problem.

### Composition of the intervention

The introduction of the NDP is considered a complex intervention. This is for intervening at different care levels, as well as for integrating a new professional into the primary work processes, which requires redistribution of tasks and responsibilities around pharmacotherapeutic care. Although the tasks of the NDP are predefined, the actual implementation in the individual GP practices cannot be protocolled: in order to increase the likelihood of a successful implementation of the intervention, the intervention has to be aligned to the needs of each participating centre. Consequently, the actual implementation of the intervention itself may be heterogeneous. This can blur quantitative measurements. Therefore, parallel to this study, we conduct a qualitative study as described earlier. With this study, we will list facilitators and barriers to the implementation process, in order to assess the feasibility of introducing a NDP in a complex healthcare setting in daily practice.

#### Development of the clinical pharmacy training program

The clinical pharmacy training program (CPTP) has been newly developed for the POINT study and has neither been validated nor accredited. As the CPTP is developed by experts in the field of education, based on the theoretical frameworks of Vermunt, Kolb and Merrienboer [27–29] and as it is embedded in the department of vocational training for general practice, it is expected to be an adequate postgraduate training for the NDPs. Within the context of the POINT intervention study, the program is evaluated and attuned on a structural basis.

### Choice of the primary outcome measurement

In the context of ‘primum non nocere’ [30] the prime aim of this study is to improve the safety of pharmacotherapy. Therefore, we chose reduction of medication-related hospital admissions (HARMs), being a severe adverse drug event, as primary outcome. This choice is, however, challenging in several aspects.

First, the incidence of HARMs in primary care is low. Although 5.6 % of acute hospital admissions are related to medication [1], this accounts for only about 3.4 medication-related hospital admissions per GP on a yearly basis – which means around 12–16 HARMs per participating practice in this study. In addition, we do have a limited follow-up period of only one year. However, our sample size calculation is based upon the occurence of HARMs in a large group, so we expect this problem to be adequately addressed. Last, measuring HARMs is challenging for quite detailed data have to be obtained in order to determine HARMs. Causality assessments in the POINT study will be based upon information of discharge letters, which is limited information. However, using this amount of information to determine HARMs has been done before [31]. Also, we do have experience from previous studies [1, 26] and will use a validated method to identify the primary outcome parameter.

### Availability of data for secondary outcome measurements

To correctly measure and analyse the secondary outcomes, the required data need to be properly documented in the GPs’ information systems. Due to the heterogeneous study setting we are dependent on the diverse working methods of the participating healthcare providers. As this possible loss of information will show equally in each research arm, we expect this will not influence our study results.

The cost evaluation performed in this study will yield an insight in the direct medical costs of each model of pharmaceutical care provision in primary care. For this evaluation, a subgroup of patients will be analysed, as data of the insurance company will not be available for all patients. A full economic evaluation including a societal costs and economic modelling is outside the scope of this research project.

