Several difficulties hamper the implementation of medication reviews in primary care [8–10] and may have contributed to the inconclusiveness of these results. First of all, as community pharmacists get no or an insufficient fee for performing medication reviews, a financial incentive is lacking. However, this does not seem to be the only problem. Another important difficulty in the implementation is the lack of information: community pharmacists do not have access to routine patient records. Consequently, performing proper medication reviews is often impeded, as not all available information can be taken into account. Third, pharmacists lack clinical pharmacology knowledge and clinical reasoning skills, for pharmaceutical training and practice are historically drug product oriented instead of patient oriented. Community pharmacists’ tasks mainly concern the organisation and monitoring of logistic processes (e.g. dispensing the right medication in the right dose to the right patient); community pharmacists perform little to no direct pharmaceutical patient care. As a result, pharmacists have sparse experience in clinical pharmacotherapy. Fourth, in the present system pharmacists and general practitioners (GPs) have different responsibilities, backgrounds and working processes, resulting in inadequate collaboration [11]. Fifth, the present way of practicing of both GPs and pharmacists is mainly reactive, while the pharmaceutical care process requires a proactive approach. Finally, there is a misfit between time-consuming nature of performing medication reviews and the current workload of both GPs and pharmacists.

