#### Group A: selecting GPs, non-dispensing pharmacists and matching both

General practices from the above mentioned networks are all pro-actively invited to participate in the POINT study. Ten general practices are selected, based on the following criteria: willingness of the GPs to participate in the project; willingness of the GPs to cooperate in the development and evaluation of the role of the NDP; minimum of 5000 registered patients; availability of an office for a NDP, with access to the GP information system; minimum of one practice nurse working on disease management programs for chronic conditions such as chronic obstructive pulmonary disease, diabetes, cardiovascular disease or mental health; healthcare centre accredited by the Dutch College of General Practitioners (NHG) [18]. The research collaboration is formalised in a collaboration agreement.

Ten non-dispensing pharmacists are employed, using a structured application procedure. All participating pharmacists have a master degree in pharmacy (PharmD) and preferably have working experience in providing pharmaceutical care to individual patients. Furthermore, in the selection procedure communication and collaboration skills, as well as pharmacotherapy knowledge, empathy, self-reflection skills and innovative attitude are emphasized.

Subsequently, each NDP is posted in one of the ten selected primary care centres in Utrecht or Amsterdam regions. The NDPs work full time and exclusively in the general practices, for a period of 15 months. The introduction of such a new role in a healthcare practice is complicated and faces a variety of challenges [14]. For example, pharmacists need to be trained to fulfil their new tasks, both pharmacists and GPs have to collaborate closely and GPs have to explore the complementary role of the NDP. Therefore, the first three months are used as a start-up period before actually starting the intervention period.

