### Individual patient consultation

The patient care process consists of an assessment of the patient’s drug-related needs, a care plan to meet the specific needs of the patient, and a follow-up evaluation to determine the impact of the decisions made and actions taken. In practice, the NDP provides pharmaceutical patient care for patients who are considered to be at risk of adverse drug events, such as HARMs. These patients, mostly of older age, with multimorbidity and polypharmacy (chronic use of five or more medicines) [1], are either pro-actively invited by the NDP or referred by the GP to discuss and review their medication. Also, patients can make an appointment for a medication assessment at their own request. During the first consultation, which is preferably a home visit, the NDP will work on a therapeutic relationship and interviews the patient to gather information on the patient’s experiences with and believes about medication, in order to assess his or her drug-related needs. Questions concern the goal of therapy for the patient, the current and past medication history, adherence to the medication regimen and patient reported medication issues. Afterwards, the NDP integrates the patient reported experiences and believes with the medical status to determine whether there are potential drug therapy problems. If necessary, the NDP provides recommendations for optimisation of pharmacotherapy to the GP: suggestions to stop, start or switch medication, to adjust dosages, or for actions to improve adherence. These recommendations result in a documented individual pharmaceutical care plan, as part of the patient’s medical record. The implementation of recommendations is monitored by the NDP. Follow-up contacts can be conducted as a home visit, a practice visit or by telephone.

Furthermore, the NDP covers other aspects of pharmaceutical patient care, such as individual consultations for specific drug therapy problems or questions, and medication reconciliation in patients discharged from hospital.

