### Quality management

The NDP aims to improve medication safety on an organisational level, through optimisation of processes within the practice around repeat prescribing, clinical care paths, administrative efficiencies and identification of common medication errors. The NDP is looking for possible optimisation options in medication regimens, such as monitoring renal function and electrolytes with indicated pharmacotherapy, tapering the chronic use of proton pump inhibitors, and optimising antibiotic prescribing. Hereby, the NDP organises targeted programs to improve the quality of pharmaceutical care in the practice. Also, the NDP provides education of patients and professionals involved.

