#### Secondary outcomes

##### Potential medication errors

The percentage of patients with potential medication errors will be measured [24]. These potential medication errors mainly concern prescription errors, such as under- and overprescribing and dosage errors. Other potential medication errors might be due to medication that is not or insufficiently effective, or to inadequate monitoring of the effects of the therapy. Also administration errors, such as non-adherence problems, will be measured as potential medication errors. A complete list of included potential medication errors can be found in Table 2.

**Table 2 Tab2:** Overview of outcomes, measurements and data sources

Outcomes	Measurement	Data sources
*Primary outcome*		
Frequency of HARMs	Number of HARMs	DL, MH, MED
Secondary outcomes		
Potential medication errors	% patients with:	
	- medication not indicated	MED/MR
	- underprescribing	MED/MR
	- dosing error (too low or too high)	MED/MR
	- therapeutic duplication medication	MED/MR
	- medication contra-indicated	MED/MR
	- drug-drug interactions	MED/MR
	- medication not effective	MED/MR
	- inadequately monitored therapy	MED/MR
	- administration errors (e.g. non-adherence)	MED/MR
Drug burden index	Drug burden of medications with sedative and/or anticholinergic effects	MR
Costs	Medication costs and healthcare-related costs	Database of insurance company

HARM hospital admission related to medication, DL discharge letter, MH medical history (with ICPC codes for diagnoses), MED medication records (including ATC code, dose and strength), MR medical records (including laboratory markers and measurements such as blood pressure, pulse and body mass index)

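### The claim that lost information is equal in each arm is unsupported and conflicts with the intervention, which can change recording in group A for the record-dependent medication-error items

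*Protocol article*

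**What the plan says.** The Discussion section on availability of data for secondary outcomes accepts that these outcomes need proper documentation in the GP systems. It adds: "Due to the heterogeneous study setting we are dependent on the diverse working methods of the participating healthcare providers". The next sentence sets the problem aside: "As this possible loss of information will show equally in each research arm, we expect this will not influence our study results".

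Elsewhere the protocol article describes how records are used and who adds to them:

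- **Group A selection.** One criterion for the practice is "availability of an office for a NDP, with access to the GP information system". The NDP works there full time.
- **Individual patient consultation.** The NDP interviews patients about medication history, adherence and problems they report. On the outcome of this, it says: "These recommendations result in a documented individual pharmaceutical care plan, as part of the patient’s medical record".
- **Quality management.** The NDP looks for improvements "such as monitoring renal function and electrolytes with indicated pharmacotherapy".
- **Groups B and C.** These practices work with community pharmacists in the traditional way. The Background says that "community pharmacists do not have access to routine patient records".
- **Outcome.** Table 2 lists nine types of potential medication error, all sourced from medication or medical records. On one of them the text says: "Also administration errors, such as non-adherence problems, will be measured as potential medication errors".
- **Data collection.** Data for both periods are extracted from the practices' electronic records after the intervention year. Nothing is obtained directly from patients.

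**The concern.** The person who delivers the intervention also adds to the record from which the outcome is read. If recording changes in group A when the NDP starts, and does not change to the same extent in B and C, a difference in recorded errors mixes safer prescribing with fuller notes.

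The bias can run either way. Asking about adherence can bring to light non-adherence that was always there, which makes group A look worse. Entering an indication or a result can remove an apparent error, which makes group A look better. A reader who accepts the equal-loss sentence would credit or blame the NDP for documentation.

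**Working it through.** The plan states no figure here, so there is none to reproduce. The check traces who writes to the record against where the outcome is read, and then illustrates the consequence.

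**1. Is equal loss consistent with the rest of the article?**

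| | Group A, after NDP start | Groups B and C |
|---|---|---|
| Pharmacist access to GP records | Yes (selection criterion) | Not described; Background says generally no |
| Pharmacist asks about adherence and history | Yes | Not described |
| Pharmacist's plan enters the medical record | Yes | Not described |
| Source of the error items | Practice medication and medical records | The same |

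Nothing in the article supports equal loss, and the group A column gives a specific reason to expect otherwise.

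**2. Do the planned comparisons remove it?** Let p be true prevalence and v the share of errors visible in the record, with no false flags. Observed prevalence is p × v. Suppose p = 0.30 everywhere and never changes, v = 0.70 in both arms before, and v = 0.80 in A and 0.70 in C afterwards.

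- Change in A: 0.30 × (0.80 − 0.70) = +3 points.
- Change in C: 0.30 × (0.70 − 0.70) = 0.
- Difference in differences: +3 points, with no true change.

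Pre-post comparison removes stable differences between practices, but this one begins with the intervention. Adjustment for baseline characteristics cannot reach it for the same reason. The confounder questionnaire does not name record completeness.

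**3. How large might it be?** The documents give no visibility figures, so p and v are assumptions. The sample size section gives at least 2,850 high-risk patients per arm, used here only for illustration. The chance of a two-sided p < 0.05 is approximately Φ(|difference|/SE − 1.96), with SE = √[(p_A(1−p_A) + p_C(1−p_C))/n]. The last column divides n by an assumed design effect of 2.8 for clustering.

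| v in A (C: 0.70) | Observed A | Observed C | Difference | Chance, no clustering | Chance, design effect 2.8 |
|---|---|---|---|---|---|
| 0.60 | 18.0% | 21.0% | −3.0 | 0.82 | 0.40 |
| 0.70 | 21.0% | 21.0% | 0 | 0.05 | 0.05 |
| 0.75 | 22.5% | 21.0% | +1.5 | 0.28 | 0.13 |
| 0.80 | 24.0% | 21.0% | +3.0 | 0.77 | 0.37 |
| 0.90 | 27.0% | 21.0% | +6.0 | >0.99 | 0.89 |

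Clustering lowers the chance of a false positive but leaves the bias unchanged.

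**4. NDP reach.** Only invited, referred or self-referred patients are seen. If visibility is 0.90 in those seen and 0.70 in the rest, and true prevalence is the same in both, arm-level v is 0.90r + 0.70(1 − r), where r is the share seen. With r = 0.25, v = 0.75; with r = 0.50, v = 0.80. The article does not give r.

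**5. The other direction.** Suppose 20% have a true error, and a missing indication falsely flags 20% of the remaining patients in C but 15% in A.

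- C: 0.20 + 0.80 × 0.20 = 36%.
- A: 0.20 + 0.80 × 0.15 = 32%.

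Group A then looks 4 points better through recording alone.

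**The case against.** The strongest reply has five parts.

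- **Control records may change too.** GPs in B and C keep records, group B pharmacists are trained in medication review, and their advice may reach the record through the GP. The line about access is general background and does not describe these particular practices. This stands. A reader might infer that recording changes in group A and nowhere else, but the documents show only that no B or C pharmacist is described as writing in the record.
- **The route from care plan to outcome is not shown.** Extraction uses standard procedures and existing algorithms, and the Table 2 footnote lists coded diagnoses, prescriptions, laboratory markers and measurements. Nothing says care-plan text is extracted, and non-adherence might be derived from prescription data. This also stands, so misclassification is likely but not demonstrated, and its size is unknown.
- **There is no defined composite.** A reader might infer one headline percentage in which opposite biases are pooled. Table 2 lists nine percentages, although the accompanying text is ambiguous.
- **Some change is real.** Better monitoring is an aim of the intervention. Only the recording part of the inadequate-monitoring item is bias.
- **A completeness table belongs in the analysis plan, which is not shown.** That is fair, and its absence is no finding. The point rests on a positive statement that the article makes.

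None of this supplies support for the equal-loss sentence.

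**Conclusion.** The equal-loss claim is unsupported and conflicts with the described intervention. The problem is differential outcome misclassification, not confounding: the intervention can change how the outcome is ascertained. It is likely for non-adherence, not indicated, not effective, underprescribing, and the recording part of inadequate monitoring. Duplication, interactions and dosing that needs no laboratory value can largely be read from prescriptions and are much less exposed.

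The direction may differ by item and the size is unknown. The spurious differences above, from −4 to +6 points, follow entirely from assumed prevalence, visibility and false-flag rates and are not estimates for this trial.

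The scope is some items of one secondary outcome. A reader might extend the point to the primary outcome, the drug burden index or costs. The sentence at issue concerns secondary outcomes, costs come from insurer data, and nothing here establishes the same bias for the other two.

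**What to change.** 1. Replace the equal-loss sentence with a statement that recording may differ by arm and period, and that the NDP may change it in group A.
2. Report completeness of ICPC codes, laboratory values and measurements by group and period.
3. Report the nine error types separately.
4. Add a prespecified analysis limited to items computable from structured prescriptions: duplication, interactions, and dosing where no laboratory value is needed. Interpret the record-dependent items as open to recording bias.
5. For contraindications, optionally add a sensitivity analysis using only diagnoses coded before the NDP start (1 March 2014 in Table 1). It should not replace the main definition, because freezing diagnoses at that date would miss contraindications arising up to 31 May 2015.

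All of this uses data already listed in Table 2. The cost is a little more analysis and a more cautious conclusion on some items of one secondary outcome.
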